### Who will take informed consent? {26a}

Patients diagnosed with aTAAD and planning to undergo surgical treatment will undergo eligibility screening to determine their suitability for participation in this trial. Once the surgeon has assessed the patient as eligible, their family will be invited to meet with the research physician. During this meeting, their family will have the opportunity to ask any questions they may have and sign the informed consent form.

### Additional consent provisions for collection and use of participant data and biological specimens {26b}

Consent will be sought for the retrospective review of participants’ medical records and the procurement of blood samples to evaluate inflammation, document adverse events, conduct comprehensive blood laboratory examinations, and analyze clinical biomarkers.

## Interventions

### Explanation for the choice of comparators {6b}

Patients diagnosed with acute type A aortic dissection (aTAAD) will be randomly allocated to either the ketorolac group or the placebo group, maintaining a 1:1 ratio. The intervention entails the administration of ketorolac tromethamine or 0.9% saline to the respective subjects. Ketorolac tromethamine, serving as the interventional treatment in the trial, will be administered 2 h prior to surgery (60 mg per 2 ml) and will continue for the initial 2 days post-operation (30 mg per 1 ml BID). The use of 0.9% saline functions as an inert placebo in the trial.

### Intervention description {11a}

The surgeries will be performed by [name]. The study will commence on the day the patients sign an informed consent form and receive their randomized numbers. The ketorolac group, consisting of patients with aTAAD, will be treated with ketorolac. They will receive a preoperative intramuscular injection of 60 mg per 2 ml ketorolac and a postoperative injection of 30 mg per 1 ml ketorolac BID for two consecutive days. The placebo group, also consisting of patients with aTAAD, will receive placebo treatment. They will receive a preoperative intramuscular injection of 2 ml 0.9% saline placebo and a postoperative injection of 1 ml 0.9% saline placebo BID for two consecutive days. During the administration of ketorolac, patients’ blood pressure and renal function will be routinely monitored, and targeted treatment methods such as sedation, hypotension, diuresis, and dialysis will be applied as necessary. Additionally, all included patients will receive the same medical and surgical treatments in accordance with the diagnosis and treatment guidelines for aTAAD. Aortic dissection tissue samples will be collected for laboratory study during the surgery. Both the ketorolac group and the placebo group patients will undergo follow-up examinations before surgery and on the 1st, 3rd, 5th, 7th, 30th, and 90th day after surgery. These examinations will include assessments of adverse drug events, cardiac ultrasound, chest X-ray, laboratory tests (blood routine examination, blood biochemistry, erythrocyte sedimentation rate, coagulation function, CK-MB, cardiac troponin I (cTnI), PCT, IL-6, CRP, myohemoglobin (MYO), type B natriuretic peptide (BNP), D-dimer, etc.) and clinical biomarkers (matrix metalloproteinase-9 (MMP-9), MMP-2, MMP-3, MMP-13, type III procollagen, etc.). CTA examination of the cervical, thoracic, and abdominal aorta artery will be performed before surgery and on the 30th and 90th days after surgery.

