#### Secondary endpoints

Erythrocyte sedimentation rate (ESR), C-reactive protein, procalcitonin, SII [17], coagulation function (prothrombin time, activated partial prothrombin time, bleeding time), liver function (alanine transaminase, glutamic transaminase, lactate dehydrogenase, total bilirubin, direct bilirubin), renal function (creatinine, uric acid, eGFR), high-sensitivity troponin T, serum B-type natriuretic peptide, myocardial enzyme (creatine kinase, creatine kinase MB isoenzyme), and other laboratory examination of blood;Chest X-ray (for pulmonary inflammation and effusion, etc.), CTA scan of the cervical, thoracic, and abdominal aorta artery (for aortic diameter and extent of dissection, etc.), cardiac ultrasound (for cardiac ejection fraction and left ventricular diastolic dysfunction, etc.), and other imaging examinations.The patient’s cardiopulmonary bypass time during surgery, total surgical time, aortic cross-clamping time, and postoperative hospital stay;Postoperative drainage color, drainage volume, postoperative patient blood transfusion, and transfusion volume;The incidence of postoperative sternal infection, secondary debridement, secondary tracheal intubation, pneumonia, and delirium; andEnzyme-linked immunosorbent assay (ELISA) will be performed to detect and measure IL-1β IL-2, IL-4, IL-6, IL-8, IL-10, IL-12, IL-13, TNF-α, INF-γ, granulocyte–macrophage colony-stimulating factor (GM-CSF) and calcitonin;

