### Participant timeline {13}

Table 1 shows the participant timeline.

**Table 1 Tab1:** Participant timeline

	Study period								
	Enrolment	Allocation	Post-allocation						Close-out
Timepoint	Before surgery	Before surgery	During surgery	Postoperative day 1	Postoperative day 3	Postoperative day 5	Postoperative day 7	Postoperative day 30	Postoperative day 90
Enrolment									
Informed consent	** × **								
Eligibility screen	** × **								
Allocation		** × **							
Randomization		** × **							
Interventions									
Tissue samples collection			** × **						
Ketorolac tromethamine		** × **		** × **	** × **				
0.9% saline		** × **		** × **	** × **				
Assessments:									
Vital signs	** × **		** × **	** × **	** × **	** × **	** × **	** × **	** × **
Hematology examination	** × **		** × **	** × **	** × **	** × **	** × **	** × **	** × **
CTA scan of cervical thoracic and abdominal aorta artery	** × **							** × **	** × **
Chest X-ray				** × **	** × **	** × **	** × **	** × **	** × **
Echocardiography	** × **				** × **			** × **	** × **
Adverse events	** × **		** × **	** × **	** × **	** × **	** × **	** × **	** × **
Complications	** × **		** × **	** × **	** × **	** × **	** × **	** × **	** × **

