### Plans for collection, laboratory evaluation, and storage of biological specimens for genetic or molecular analysis in this trial/future use {33}

All patients will provide aortic dissection tissue samples during surgery, which will be sent to the laboratory for hematoxylin–eosin staining, western blot, and immunofluorescence. Additionally, blood samples will be collected before surgery and at 1, 3, 5, and 7 days after surgery. These blood samples will also be sent to the laboratory for ELISA. The tissue specimens will be stored at room temperature after being embedded in paraffin or frozen in liquid nitrogen and stored in a refrigerator at − 80 ℃. Similarly, the blood samples will be centrifuged and stored in a refrigerator at − 80 ℃.

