### Methods in analysis to handle protocol non-adherence and any statistical methods to handle missing data {20c}

We allow patients to have 10% missing data, which will be deleted as blank. When the patient’s data is missing by more than 10%, the patient will be deleted.

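### The text, Table 1, the blood-sampling plan and the endpoint list disagree on what is measured and when, and the 10% missing-data deletion lets that disagreement affect who is in the primary analysis

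*Protocol article*

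**What the plan says.** - **Intervention description {11a}.** Both groups have "follow-up examinations before surgery and on the 1st, 3rd, 5th, 7th, 30th, and 90th day after surgery". On content: "These examinations will include assessments of adverse drug events, cardiac ultrasound, chest X-ray, laboratory tests", and then clinical biomarkers (four MMPs and type III procollagen). Only CTA gets days of its own: it "will be performed before surgery and on the 30th and 90th days after surgery". The laboratory list includes cardiac troponin I.
- **Participant timeline {13}, Table 1.** The row "Echocardiography" is marked before surgery and on days 3, 30 and 90. Chest X-ray is marked on days 1, 3, 5, 7, 30 and 90. The row "Hematology examination" is marked at all seven text times and also during surgery. There is no biomarker or ELISA row.
- **Biological specimens {33}.** For laboratory work by ELISA, "blood samples will be collected before surgery and at 1, 3, 5, and 7 days after surgery".
- **Secondary endpoints.** The troponin endpoint is "high-sensitivity troponin T". The ELISA endpoints are a cytokine panel and calcitonin; MMPs and procollagen are not named.
- **Missing data {20c}.** When a patient's data "is missing by more than 10%, the patient will be deleted". Statistical methods {20a} gives this deletion as the reason for having no intention-to-treat analysis.

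**The concern.** Four places in the current text each give explicit content, and they do not agree. This is not brevity, because the article states days and assays and states them differently. Taken alone, these would be points to tidy up in secondary measurements.

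The deletion rule makes them matter more. It works on a percentage of missing data, and a percentage needs a list of what was expected. If the seven-visit text is that list, examinations never scheduled in Table 1 count as missing. If Table 1 is the list, they do not. Deletion removes the patient altogether, so the choice can affect the primary composite as well as the secondary endpoints. If it is made after data have been seen, it becomes a freedom to choose the primary analysis set.

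The timing adds some urgency. Trial status reports 55 patients included by 20 March 2024, and the interim analysis is set at 60.

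**Working it through.** **Reproducing the plan's figure.** The plan gives no count of expected measurements, so nothing of that kind can be reproduced. Its sample size does reproduce with unpooled variance: (1.960 + 1.2816)² × (0.21 + 0.24) / 0.09 = 52.5, so 53 per arm. This point does not change it.

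**Schedules side by side**

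| Item | Text {11a} | Table 1 or sampling plan | Difference |
|---|---|---|---|
| Echocardiography | 7 times | 4 (Table 1) | 3 (days 1, 5, 7) |
| Chest X-ray | 7 times | 6 (Table 1) | 1 (before surgery) |
| Routine blood tests | 7 times | 8 (Table 1) | 1 extra, during surgery |
| Biomarker blood | 7 times | 5 (sampling plan {33}) | 2 (days 30, 90), if the plan covers them |
| CTA | 3 times | 3 (Table 1) | none |
| Troponin | I | T (Secondary endpoints) | different analyte |

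**Share of the text's items absent for a patient who complies fully with Table 1 and the sampling plan.** The denominator is not defined, so two ways of counting are assumed.

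*One item per examination per visit.* Adverse events 7 + echocardiography 7 + X-ray 7 + laboratory 7 + biomarkers 7 + CTA 3 = 38.
- Echocardiography and X-ray only: (3 + 1)/38 = 10.5%.
- With biomarkers stopping at day 7: (3 + 1 + 2)/38 = 15.8%.

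*One item per named analyte per visit.* The text names 12 laboratory tests and 5 biomarkers: 7 × 3 + 12 × 7 + 5 × 7 + 3 = 143.
- Echocardiography and X-ray only: 4/143 = 2.8%.
- With biomarkers stopping at day 7: (4 + 5 × 2)/143 = 14/143 = 9.8%.

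**Near the limit.** Ten per cent of 143 is 14.3 items. A patient already lacking 14 by design crosses the limit with one more missing value (15/143 = 10.5%). Counted only against what was scheduled, 143 − 14 = 129 items, the same patient crosses it at 13 missing values (13/129 = 10.1%; 12/129 = 9.3%).

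**Scale of a loss, for illustration only.** With 70% against 40% events and unpooled variance, power is 93.4% at 60 per arm, 90.8% at 54 and 87.3% at 48. The documents give no basis for predicting how many patients would be deleted.

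**The case against.** The strongest reply is that no sensible analyst would count a never-scheduled test as missing, since on some counts that would delete every participant. The denominator of a missing-data rule is also often left to the analysis plan. Much of this stands: wholesale deletion is not a realistic forecast. What remains is that the published text, not only the table, schedules those tests, and the rule does not say which governs.

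The size is also soft. On the analytes that the text itself names, the share stays below 10%. Demographic data, vital signs and complications, if counted, would enlarge the denominator and lower every percentage. A higher figure is tempting but unsupported. Leaving out adverse-event assessments gives 6/31 = 19%, yet they come first in the text's list. Counting the endpoint list's laboratory variables and ELISA panel at seven visits gives 38/269 = 14%, yet no section places that panel at seven visits.

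A reader might also infer the following, which the documents do not show:
- **That troponin T is not measured.** The text's laboratory list is open-ended. The assay is absent from the stated list, which does not prove that it is not run.
- **That the biomarker endpoints have no day-30 or day-90 value.** The ELISA panel is consistent with its own plan to day 7. Applying those days to the MMPs and procollagen is an inference, because the sampling plan names ELISA but not those analytes.
- **That the X-ray endpoint fails for want of a baseline.** The planned tests compare randomised arms, so a postoperative comparison needs none.

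**Conclusion.** The inconsistency is real and lies in the current text: echocardiography at seven times against four, chest X-ray at seven against six, an intraoperative blood test in Table 1 only, troponin I against troponin T, and biomarkers to day 90 against a research blood plan to day 7 of unstated scope.

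Its consequence is limited but not trivial. A patient who complies fully with Table 1 and the sampling plan lacks roughly 3% to 16% of the text's items. The range spans the 10% limit, so the expected-data list can affect membership of the primary analysis set. The range rests on two assumed ways of counting, on applying the sampling plan's days to the MMPs and procollagen at its upper values, and on Table 1 as read from extracted text. The dependence on the schedule is firm; its size is not. The documents do not support saying that compliant patients will be deleted, or that any endpoint goes wholly uncollected.

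No primary component, as listed under Outcomes, is defined by an echocardiogram, a chest X-ray or a troponin value. Losing a patient from the primary analysis over one of these would therefore be avoidable.

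**What to change.** 1. Reconcile the Intervention description, Secondary endpoints, Table 1 and the specimen section into one schedule. Table 1 cannot simply be declared the master. It needs a biomarker/ELISA row with sampling days that says whether the MMPs and procollagen are included. Its own conflicts with the text must also be resolved: the intraoperative blood test, and the study-drug marks at postoperative days 1 and 3 where the abstract gives the first and second postoperative days.
2. Name the one troponin assay actually run, identically in the visit list and the endpoint list.
3. Count missing data only against the reconciled schedule.
4. State that missing laboratory or imaging measurements do not remove a randomised patient from the primary clinical-event analysis.

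The cost is a correction to wording and one table, with no new tests, best settled before interim data are examined. The downside is that some endpoints may lose days that the text promised.

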### Criteria for discontinuing or modifying allocated interventions {11b}

Subjects can withdraw from the study at any time for any reason. Considering the safety of the subjects. When the subject experiences situations where it is not appropriate to continue the study, including worsening of the condition, serious adverse events, poor compliance, experiencing intolerable accidents such as bankruptcy or family misfortune, and unwillingness to sign an informed consent form. Patients can be terminated to continue this study.

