### Outcomes {12}

#### Primary endpoint

Efficacy: death, organ malperfusion syndrome, permanent dialysis, tracheotomy, neurological impairment, postoperative mechanical circulatory support, and unplanned cardiac reoperation.

Safety: gastrointestinal ulceration, gastrointestinal bleeding, gastrointestinal perforation, postoperative hemorrhage (postoperative hemorrhage exceeding 1000 ml within 24 h), renal failure, liver failure, drug allergies, and other severe adverse events following drug administration.

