### Procedure for unblinding if needed {17b}

Emergency unblinding can be performed at any time if patients experience severe adverse events or unexpected worsening of their clinical status, as deemed necessary by the principal investigator or the sponsor. Participants are provided with “In case of emergency” cards, which should be carried at all times during the study and include an emergency phone number. The researcher must record the date, location, reason, person responsible for unblinding, main investigator, and relevant personnel in charge of the drug clinical trial institution. These details should be documented in the case report form (CRF). Subjects who undergo emergency unblinding will be considered as withdrawal cases.

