## Data collection and management

### Plans for assessment and collection of outcomes {18a}

Clinical data, including patient admission information, demographic data, laboratory blood examinations, and imaging examinations, will be collected from the electronic medical record (EMR). The CRFs will be initially filled out on paper and then entered into Microsoft Excel by the associated researchers. The follow-up period will last for 90 days, during which the researchers will record all medical data and laboratory results from any hospital visits. At the end of the follow-up period, the patients will be interviewed via telephone.

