## Statistical methods

### Statistical methods for primary and secondary outcomes {20a}

Statistical analysis will be performed using SPSS software (version 26.0) and R (× 64 3.5.0). Continuous variables will be presented as mean ± standard deviation. The Kolmogorov–Smirnov test will assess normal distribution. If variables exhibit normal distribution, an independent sample *t*-test will be employed; otherwise, the Mann–Whitney *U* test will be utilized. Categorical variables’ frequency will be expressed as percentages and analyzed using the chi-square test or Fisher’s exact test. It should be noted that we are not conducting an Intention to Treat analysis due to the exclusion of patients with more than 10% missing data. Double-tailed *p*-values and 95% confidence intervals will be reported, with statistical significance defined as *p* < 0.05.

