### Adverse event reporting and harms {22}

Any adverse events (AEs) that occur during the study period will be carefully documented, evaluated, and treated. AEs grading will be based on Common Terminology Criteria for Adverse Events V.5.0.In the case of serious AEs that pose a risk to the patient’s life, an immediate report will be submitted to the Medical Ethics Committee of Affiliated Nanjing Drum Tower Hospital, Nanjing University Medical College. Additionally, the incidence of AEs will be calculated.

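### Patients ended from the study or unblinded because of a serious event can be deleted from the primary comparison under the 10% missing-data rule, even when their primary event was already observed

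*Protocol article*

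**What the plan says.** Section {11b} is headed as criteria for discontinuing or modifying the intervention, but its text is about leaving the study. Its reasons include "worsening of the condition, serious adverse events, poor compliance", and the consequence is "Patients can be terminated to continue this study". It has no rule for stopping the injections while the patient stays under observation.

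Section {17b} allows emergency unblinding for severe adverse events or unexpected worsening, where the principal investigator or sponsor judges it necessary. It then states: "Subjects who undergo emergency unblinding will be considered as withdrawal cases".

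The primary endpoint has an efficacy and a safety composite. The safety composite includes "other severe adverse events following drug administration".

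Section {20a} says "we are not conducting an Intention to Treat analysis due to the exclusion of patients with more than 10% missing data". Section {20c} repeats the rule: where a patient's "data is missing by more than 10%, the patient will be deleted". Neither section exempts a patient in whom a primary event has already been recorded, and neither says what the 10% is a percentage of.

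Two statements point the other way. Section {18a} says that over the 90 days "the researchers will record all medical data and laboratory results from any hospital visits". Section {22} says that "the incidence of AEs will be calculated".

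**The concern.** Three stated rules form a chain. A serious event can end participation, or lead to unblinding and so to withdrawal status. Ended participation can produce missing visits. Missing visits above 10% remove the patient from the analysis. The first link is itself a primary outcome, so the patient and the event can leave the comparison together.

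That is selection on the outcome after randomization, and randomization no longer protects the comparison of the patients who remain. The separate adverse-event incidence in section {22} does not return a deleted patient to the primary endpoint.

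The deletion rule is the operative defect. Sections {11b} and {17b} delete no one; they supply a route by which event patients in particular can meet the rule. A patient who dies early could also meet it without either section, if assessments after death are counted as missing. The protocol does not say whether they are.

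**Working it through.** **1. The plan's own figure.** Section {14} assumes 70% v 40% events and gives 53 per arm, raised to 60. With two-sided alpha 0.05, power 90% and unpooled variance: (1.960 + 1.282)² × (0.7×0.3 + 0.4×0.6) / 0.3² = 10.51 × 0.45 / 0.09 = 52.5, so 53. Sixty per arm allows a loss of 7/60 = 11.7%, in line with the stated loss above 10%. The figure reproduces and is not at fault.

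**2. Does an exit exceed 10% missing?** The denominator is undefined, so three counts are tried. All assume that data collection stops with participation.

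- *Table 1 assessment marks, counted equally.* Vital signs 8, hematology 8, CTA 3, chest X-ray 6, echocardiography 4, adverse events 8, complications 8; total 45. From day 3 on: 6 + 5 + 5 + 7 + 7 = 30.
- *Scheduled examinations in section {11a}.* Before surgery and days 1, 3, 5, 7, 30 and 90; total 7.
- *Individual variables (assumed listing).* 17 laboratory and biomarker items × 7 visits = 119; 12 ELISA analytes × 5 times = 60; 45 − 8 = 37 other Table 1 marks; 13 operative and postoperative items; total 229. Lost from day 3 on: 17×5 + 12×3 + 25 = 146. Lost at days 30 and 90: 2 × (17 + 6) = 46. Lost at day 90: 23.

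| Data missing | Table 1 marks | Examinations | Variables |
|---|---|---|---|
| From day 3 on | 30/45 = 67% | 5/7 = 71% | 146/229 = 64% |
| Days 30 and 90 | 14/45 = 31% | 2/7 = 29% | 46/229 = 20% |
| Day 90 only | 7/45 = 16% | 1/7 = 14% | 23/229 = 10.04% |

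The first two rows exceed 10% on every count. The third does not do so reliably: one more baseline item gives 23/230 = 10.0%, which is not above 10%.

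**3. Effect on one arm's rate.** With true rate p, and shares fe of event patients and fn of event-free patients deleted, the observed rate is p(1−fe) / [p(1−fe) + (1−p)(1−fn)]. Assume p = 20%.

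- fe = 25%, fn = 0: 0.15/0.95 = 15.8%, too low.
- fe = fn: 20%, unchanged.
- fe = 10%, fn = 20%: 0.18/0.82 = 22.0%, too high.

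**4. Effect on the harm comparison.** Assume 20% v 10% (true odds ratio 2.25) and fn = 0.

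- fe = 25% in both arms: 15.8% v 7.7%, difference 8.1 points. fe = 75% in both: 5.9% v 2.7%, difference 3.2 points. The odds ratio stays 2.25.
- fe = 50% v 25%: 11.1% v 7.7%, odds ratio (0.10/0.80)/(0.075/0.90) = 1.50.
- fe = 25% v 50%: 15.8% v 5.3%, odds ratio (0.15/0.80)/(0.05/0.90) = 3.38.

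**5. Effect on efficacy.** Section {14}'s rates, 60 per arm, fn = 0; deletion shares of 10%, 20% and 30% are assumed.

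- No true effect (70% in both arms), ketorolac event patients deleted only: 0.63/0.93 = 67.7%, 0.56/0.86 = 65.1%, 0.49/0.79 = 62.0%. The apparent benefit is 2.3, 4.9 or 8.0 points, and the two-sided error rate about 5.8%, 8.6% or 14.1%.
- True 70% v 40%, placebo event patients deleted only: difference 27.7, 25.1 or 22.0 points; power falls from 92% to 86%, 76% or 62%.
- True 70% v 40%, ketorolac event patients deleted only: difference inflated to 32.5, 35.2 or 38.2 points.

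**The case against.** The chain is conditional. Termination under section {11b} is permissive, and unblinding needs a judgement that it is necessary. Section {11a} plans examinations to day 90 for both groups. Section {18a} adds hospital records and a closing telephone interview, and adverse events are documented throughout. None of this is limited to patients still on drug. A condensed article may also leave follow-up after discontinuation to the full protocol. So a reader might infer that every patient with a serious event will be deleted, and the text does not support that. What remains is that none of these provisions is said to cover withdrawn patients, while withdrawal status, the rejection of intention to treat and deletion above 10% are all stated outright. They are not details left to an analysis plan, and an analysis plan cannot recover follow-up that was allowed to stop.

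A reader might also infer that harm rates must read too low in both arms. That holds only if event patients are deleted more often than event-free ones. The 10% rule also removes event-free patients who miss visits, and section {11b} lists exits unrelated to events; step 3 shows the rate can move up.

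A third inference is that the sample size has almost no room: 60 − 53 = 7, less a 10% loss of 6, leaves 1. This assumes that these exits come on top of the planned loss. The allowance may already contain them, so no shortfall is shown.

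Finally, dosing ends after the second postoperative day. Separating drug stop from study exit therefore matters mainly for early events, although later unblinding still confers withdrawal status.

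**Conclusion.** The point stands in a limited form. As written, the protocol permits a patient to leave the primary comparison because of an event that it is meant to count, including an event already observed. Early exit, or loss of both late visits, exceeds the 10% limit on each count tried, provided that data collection ends with participation. Day 90 alone is undecided while the denominator is undefined.

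The document gives no exit rate, so the bias can be neither sized nor signed. Harm rates read too low if event patients are deleted more often than event-free patients. The between-arm comparison can be biased either way if deletion differs by arm. The figures in steps 3 to 5 illustrate the mechanism under assumed deletion shares, and in steps 3 and 4 under assumed event rates; they do not forecast this trial. The deletion rule and the rejection of intention to treat are the operative faults, with the exit and unblinding wording contributing to them.

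**What to change.** - **Section {11b}:** keep the right to withdraw. Replace the text from the sentence that lists the situations to the end of the section with: *If the condition worsens, a serious adverse event occurs, or compliance is poor, study drug can be stopped. The patient stays in follow-up to day 90 unless consent to follow-up is withdrawn. The date and reason are recorded in the CRF.* Changing only the final sentence would leave the preceding text, which calls continuation in the study inappropriate, in conflict with continued follow-up.
- **Section {17b}:** replace the last sentence with: *Emergency unblinding ends study drug, not follow-up.*
- **Sections {20a} and {20c}:** state that the primary efficacy and safety composites are analysed in all randomized patients in their allocated group, that events before or after stopping study drug count, and that the 10% deletion rule does not apply to these endpoints. Remove the rejection of intention to treat for them. Handling of patients with no observed event and incomplete follow-up can go to the analysis plan.

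The cost is a wording amendment, slightly more follow-up and one CRF line. Dosing and the 60 per arm do not change, so the 55 patients included by March 2024 and the remaining 120 − 55 = 65 stay on one regimen. For patients who have already exited, events can be sought from the medical record and the closing telephone interview, where consent allows. The downside is that the estimate includes patients who received fewer injections. Settle the change before the interim data at 60 patients are seen.
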